##### Dual-energy x-ray absorptiometry

Dual-energy x-ray absorptiometry (DXA) was used to measure percentage of total fat mass (TFM%), percentage of android fat (AF%), the android gynoid ratio (A/GF) and lean mass (kg), using a GE Lunar Prodigy apparatus (GE Healthcare, Madison, Wisconsin, USA). All DXA scan analyses were performed at the Faculty of Physical Activity and Sport Sciences using GE Encore 2002 software v 6.10.029.

##### Nuclear magnetic resonance

Nuclear Magnetic Resonance (MRI) was used to study the proportion and location of the adipose tissue. The MRI study measured changes at different abdominal adipose tissue compartments: SAT (superficial and deep depots) and VAT (intraperitoneal and retroperitoneal compartments). Images were obtained with a GE Medical Systems 1.5 Tesla whole body scanner using a T1-weighted fast-spin echo pulse sequence at the University Hospital *La Paz* Research Institute. The subjects were examined in supine position with arms positioned parallel along the lateral sides of the body. The subjects were imaged in two half-body volumes. A breath-hold sequence during expiration (approximately 20 seconds per acquisition) was used to minimize the effects of respiratory motion on the images. The total research time was about 5-10 min. All images were acquired on a 256x192 matrix, 16 bits/pixel, with a field of view = 480 mm. Slice thickness was 6 mm and contiguous slices were obtained every 1.5 mm from de first sacral vertebra upwards, until to achieve 30 images per person. For each subject six reference levels were studied, corresponding to intervertebral disc levels L5-S1 to L2-L3, at umbilical and at caudal left kidney positions. The acquired axial MR images were retrieved from the scanner using the DICOM^®^ protocol and after were transferred to an external personal computer running Windows XP. We used specially designed image analysis software Stereonauta for quantitative analysis of the images.

#### Biochemical, metabolic, inflammatory and genetic profile

##### Biomarkers

Blood samples were taken early in the morning at the La Paz University Hospital Extraction Unit after a 12 h overnight fast by venipuncture from the antecubital vein. Samples were kept at 4- 6°C until analysis, which was always performed within 48 h following standard hospital procedures. The following parameters were measured:

•Hematology was performed in a Pentra 120 DX cell counter (ABX-Horiba, Montpellier, France).

•Serum calcium, phosphorus, total proteins, albumin, creatinine, uric acid, bilirrubin, lipase, alkaline phosphatase, creatinkinase, LDH, GOT and GPT were analyzed by enzymatic-spectrophotometric assay (Olympus AU 5400, Izasa, Porto, Portugal).

•Blood lipid profile (total cholesterol, HDL and LDL cholesterol, triglycerides) and glucose were analyzed by means of a enzymatic-spectrophotometric assay (Olympus AU 5400, Izasa, Porto, Portugal). Apo A and Apo B were determined using a BNII nephelometer (Siemens Healthcare Diagnostics GmbH, Eschborn, Germany). Atherogenic risk ratios were calculated: total cholesterol/HDL, LDL/HDL and Apo B/Apo A1.

•Plasma fasting inmunoreactive insulin was measured by enzymatic method in a fluoro-immunochemistry Analyzer (AIA-360, Tosoh Bioscience, Tessenderlo, Belgium). Insulin sensitivity was estimated using the HOMA-IR index [HOMA-IR = fasting glucose (mmol/l)/fasting immunoreactive insulin (mU/ml)/22.5].

•Inflammatory biomarkers: Plasma C-reactive protein concentrations (CRP) were determined using a BNII nephelometer (Siemens Healthcare Diagnostics GmbH, Eschborn, Germany). Plasma fibrinogen was measured by coagulometric methods (ACL TOP 700, Izaasa, Porto, Portugal). Plasma leptin, IL-6 and TNF-α plasma concentrations were determined using a Luminex^®^-LX200 Analyzer (Millipore Corp, Billerica, Massachusetts, USA) and a MILLIPLEX MAP human circulating cancer biomarker magnetic bead panel (HCCBP1MAG-58 K) (Millipore, St. Charles, Missouri, USA). All samples were analyzed in duplicate. Data were analyzed using 3.1 xPONENT Software (Millipore, St. Charles, Missouri, USA). The intra and inter-assay coefficients of variation for the cytokine assays all fell in the 5-10% range.

•25-hydroxyvitamin D was measured by chemiluminescent immunoassay using the LIAISON” Analyzer family (Palex Medical, Barcelona, Spain).

•Serum TSH was measured by an electrochemiluminescence immunoassay (ECLIA) by using an E170 analyser (Roche Diagnostics, Mannheim, Germany).

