**Methods/design:**

One-hundred nineteen overweight (46 males) and 120 obese (61 males) subjects aged 18–50 years were randomly assigned to a strength training group, an endurance training group, a combined strength + endurance training group or a diet and physical activity recommendations group. The intervention period was 22 weeks (in all cases 3 times/wk of training for 22 weeks and 2 weeks for pre and post evaluation). All subjects followed a hypocaloric diet (25-30% less energy intake than the daily energy expenditure estimated by accelerometry). 29–34% of the total energy intake came from fat, 14–20% from protein, and 50–55% from carbohydrates. The mayor outcome variables assesed were, biochemical and inflamatory markers, body composition, energy balance, physical fitness, nutritional habits, genetic profile and quality of life. 180 (75.3%) subjects finished the study, with a dropout rate of 24.7%. Dropout reasons included: personal reasons 17 (28.8%), low adherence to exercise 3 (5.1%), low adherence to diet 6 (10.2%), job change 6 (10.2%), and lost interest 27 (45.8%).

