### Inclusion and exclusion criteria

Inclusion criteria included being male or female living in the Region of Madrid, being overweight (BMI 25–29.9 kg/m^2^) or obese (BMI: 30–34.9 kg/m^2^), middle-aged (from 18 to 50 years), having a sedentary lifestyles (< 30 min Physical Activity/day), being normoglycaemic, and non-smoker [37,41]. In the case of females, having regular menstrual cycles was required.

The exclusion criteria were suffering from a physical (orthopaedic limitations, stroke, etc.) and/or psychological (anorexia, bulimia, etc.) disease that may have precluded the performance of the requested strength or endurance training, intake of any medication (beta blockers, alcohol, etc.) known to influence physical performance or the interpretation of the results, having a history of systematic strength or endurance training (moderate to high intensity training more than once a week) in the year before the beginning of the study [37,40].

After the intervention period, participants who failed to comply with 90% assistance to the training sessions and less than 80% adherence to the diet were excluded from further analysis. The characteristics of the final sample (completers) are shown in Table 1.

**Table 1 T1:** Baseline data (n = 180)

	**Overweight n = 84**		**Obesity n = 96**	
	**Women**	**Men**	**Women**	**Men**
	**n = 48**	**n = 36**	**n = 48**	**n = 48**
Age (years)	37.29 ± 8.25	37.42 ± 8.02	39.02 ± 7.74	38.79 ± 7.99
Body Weight (kg)	73.5 ± 5.87	88.21 ± 8.13	88.33 ± 10.1	102.04 ± 8.94
Height (m)	1.62 ± 0.06	1.75 ± 0.07	1.64 ± 0.07	1.77 ± 0.06
BMI (kg/m^2^)	28.01 ± 1.32	28.57 ± 1.12	32.41 ± 1.85	32.4 ± 1.9
Body fat (%)	43.28 ± 3.62	33.8 ± 4.63	47.11 ± 3.49	38.17 ± 4.02
Body fat free mass (kg)	40.25 ± 4.3	55.99 ± 5.47	44.3 ± 4.71	58.63 ± 8.96
Bone mineral density (g/cm^2^)	1.18 ± 0.1	1.26 ± 0.09	1.21 ± 0.11	1.3 ± 0.1

Results are shown as Mean ± SD.

*Note*. BMI = Body Mass Index. Body fat, Body fat free mass and Bone mineral density calculated by Dual-energy x-ray absorptiometry (DXA).

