### Statistical analysis

The main independent variables of the study were: intervention group, age, gender, measurement (baseline – post) and BMI classification (overweight or obese). The delta percentage was calculated thought the standard formula: change (%) = [(post-test score − pre-test score)/pre-test score]*100. The power calculated previously to find significant differences between groups was 0.8 to fat mass (%).

Standard statistical methods will be used for the calculation of the means and standard deviation for all dependent variables. The statistical analysis will be as follows: 1) Univariate descriptive analysis, study of data distribution, basic statistics such as central and dispersion values. Pair comparison tests with previous analysis of the homogeneity of variance will be used. Pearson correlation coefficients, chi-squared tests and exact probability calculations will be also performed to study the relationship between quantitative and qualitative variables, respectively; 2) General lineal models, such a multivariate analysis (MANOVA) or two way analysis of variance (ANOVA) for repeated measures, will be used to determine differences among the four interventions groups and between baseline and post-training values. Compound symmetry, or sphericity, will be verified by the Mauchly test. When the assumption of sphericity would not be met, the significance of F ratios will be adjusted according to the Greenhouse-Geisser procedure. Multiple comparisons of ANOVAs will be made with the Bonferroni post -hoc test.

The analysis of the data will be done using statistical package SPSS (SPSS Inc., Chicago, Illinois, USA). The significant level will be set at α = 0.05.

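### HOMA-IR is printed as glucose divided by insulin rather than multiplied by it; applied as printed, the index would usually move opposite to insulin resistance

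*Protocol article*

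**What the plan says.** The Biomarkers section says of the assay that "Plasma fasting inmunoreactive insulin was measured by enzymatic method in a fluoro-immunochemistry Analyzer". It then says that "Insulin sensitivity was estimated using the HOMA-IR index" and gives the formula in square brackets: "HOMA-IR = fasting glucose (mmol/l)/fasting immunoreactive insulin (mU/ml)/22.5". The formula appears nowhere else in the article, and no HOMA-IR values are reported.

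Three other places bear on its use:

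- The abstract's Methods/design paragraph lists the major outcomes as "biochemical and inflamatory markers, body composition, energy balance, physical fitness, nutritional habits, genetic profile and quality of life". HOMA-IR falls within the biochemical class but is not named there.
- The Inclusion and exclusion criteria require "being normoglycaemic, and non-smoker" status, so fasting glucose should vary over a narrow range.
- The Statistical analysis section defines the change score as "change (%) = [(post-test score − pre-test score)/pre-test score]*100".

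**The concern.** HOMA-IR is a fixed, named index that rises with both fasting glucose and fasting insulin. The printed version has a division sign where the multiplication sign belongs, so it rises with glucose but falls with insulin. The printed insulin unit, mU/ml, is also 1000 times too large for the constant 22.5.

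The trial aims to identify the most effective training programme under caloric restriction, and results on individual health parameters are left to later publications. Those papers may refer back to this article for their methods. If the printed rule were followed, an arm in which insulin fell could be reported as having become more insulin resistant, and the ordering of arms on this marker could be turned round.

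**Working it through.** **Inputs.** From the article: the printed formula, the constant 22.5, the normoglycaemia criterion and the percent-change formula. The article states no glucose, insulin or HOMA-IR figure, so there is none to reproduce. All glucose (G, mmol/l) and insulin (I, microU/ml) values below are assumed and only illustrate the algebra. The product definition is the generally known one.

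**1. Does the printed form fit its own constant?** 22.5 = 4.5 × 5, so it scales a product to 1 at G = 4.5, I = 5:

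- Product: 4.5 × 5 / 22.5 = 1.00
- As printed: 4.5 / 5 / 22.5 = 0.040

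The constant has a natural role in the product and none in the quotient. The label IR (resistance) also fits only a form that rises with insulin.

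**2. Direction in insulin, at G = 5.0.**

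| I | Product | As printed |
|---|---|---|
| 5 | 1.11 | 0.044 |
| 10 | 2.22 | 0.022 |
| 20 | 4.44 | 0.011 |

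Halving insulin from 20 to 10 halves the product and doubles the printed value.

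**3. Percent change from baseline.**

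| G | I | Product | As printed |
|---|---|---|---|
| 5.2 to 5.0 | 12 to 9 | -27.9% | +28.2% |
| 5.5 to 5.2 | 15 to 10 | -37.0% | +41.8% |
| 5.5 to 4.5 | 10 to 9.5 | -22.3% | -13.9% |

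First row in full: product (5.0 × 9)/(5.2 × 12) - 1 = 45/62.4 - 1 = -27.9%; printed (5.0/9)/(5.2/12) - 1 = 0.5556/0.4333 - 1 = +28.2%.

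**4. When does the sign flip?** Let a and b be the changes in ln G and ln I. The product changes by a + b on the log scale and the printed form by a - b. Their signs differ exactly when (a + b)(a - b) = a² - b² is negative, that is, when insulin changes proportionally more than glucose. The third row of the table fails this condition, and both forms fall.

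**5. Ranking of participants.** With log-scale SDs sG and sI and log-scale correlation r, the correlation between the logs of the two forms is

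(sG² - sI²) / √[(sG² + sI²)² - 4(r sG sI)²], where s² = ln(1 + CV²).

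| CV of G | CV of I | r | Correlation |
|---|---|---|---|
| 8% | 50% | 0 | -0.94 |
| 8% | 50% | 0.3 | -0.95 |
| 8% | 30% | 0.3 | -0.87 |
| 10% | 30% | 0.5 | -0.83 |
| 8% | 60% | 0.4 | -0.97 |

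Across these assumed settings the ordering is nearly reversed.

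**6. Unit.** Read literally, 12 microU/ml is 0.012 mU/ml, and the printed formula at G = 5.2 gives 5.2 / 0.012 / 22.5 = 19.3 instead of 0.0193. A constant factor of 1000 changes the reported level but cancels in the percent change.

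**The case against.** The strongest reply is that this may be only a misprint. The name and the constant both point to the product, so the authors may well have computed it correctly and mistyped one operator. The article contains no syntax and no HOMA-IR result. That stands, and it limits the finding to a wrong definition with a conditional consequence. It does not make the definition right. Loss of the sign in text conversion is unlikely, because multiplication signs survive in the adherence formulas and in the change formula. The unit is less certain: a micro sign could have been turned into an m.

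A reader might infer that the trial's conclusions on insulin resistance are reversed. The article does not support that. It reports no such conclusion and does not show that the quotient was used. Even if it was, the sign need not flip when glucose falls proportionally more than insulin.

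Two further replies also stand. The unit error does not alter percent change, so it is a matter of notation. Speaking of sensitivity while using a resistance index is not a separate error, since the two are inverse descriptions of one property. It does leave the reader without a stated direction, and the quotient next to it points the wrong way for an index called IR.

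Finally, HOMA-IR is one derived index in a long panel. Glucose and insulin are measured separately, so no data are lost and the index can be recalculated at any time.

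**Conclusion.** The printed definition is wrong in its operator, and no other part of the article corrects it. If followed, it would usually turn an improvement into an apparent worsening: about +28% instead of -28% in one assumed example, and a log-scale correlation of about -0.83 to -0.97 with the proper index under the assumed variation. Those sizes rest on assumed glucose and insulin values, and on insulin varying proportionally more than glucose, which the normoglycaemia criterion makes likely but not certain. That insulin falls during the trial is also an assumption; the article does not say so.

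The scope is this one biomarker. The sample size and the 80% power are set for percentage body fat and are unaffected. Should-fix.

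**What to change.** - Restate the formula as HOMA-IR = fasting glucose (mmol/l) × fasting insulin (microU/ml) / 22.5. This corrects the operator and, as a notation point, the unit.
- Describe the index as a measure of insulin resistance and state that higher values mean more resistance.
- Check the syntax used on the database. Recompute the variable, and anything derived from it, only if the quotient was applied.

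The cost is one line of text and one syntax check, with one recomputed variable at most. No new data are needed, because glucose and insulin are both measured.

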##### Genetic profile

We investigated the potential influence of different genetic single nucleotide polymorphisms (SNPs), highly prevalent in the general population, on the response to different training protocols in overweight and obesity treatment. These SNPs are located in genes involved in metabolic pathways related to adiposity (Beta-Adrenergic and Leptin receptors, and Peroxisome Proliferator-Activated Receptor), and in genes involved in energy metabolism and the production of energy during physical activity (metabolism of lactate and fatty acids). In addition, we have studied the Angiotensin-Converting Enzyme (ACE) Insertion/Deletion (I/D) polymorphism, which has been associated with athletic performance and training adaptation. The potential role for most of the selected polymorphisms is well documented, both as overweight/obesity risk factors and as modulators for the response to different interventions.

With regard to the method used, we firstly reviewed published literature about the techniques for analyzing the polymorphisms [59-68]. Then, we adapted these protocols to the conditions in our laboratory. Whole blood (5 ml) from each patient was collected in EDTA and sent to the Metabolism, Genetics and Nutrition Research Group of the School of Medicine-IFIMAV, in Santander. DNA was extracted from each sample using the “QIAamp^®^ DNA Blood Mini Kit” from QIAGEN (Hilden, Germany) and the genotyping was performed for each SNP afterwards. The DNA samples were preserved at −40°C. All subjects signed a specific informed consent which allows storage and genetic characterization in relation to the objectives of the PRONAF study by the Metabolism, Genetics and Nutrition Research Group of the IFIMAV following the protocols of confidentiality and clinical safety, ensuring the anonymity of the samples and their use for research only.

After selecting the most interesting SNPs for the project objectives, the analyses were performed using genotyping assays based on techniques of double PCR, PCR and RFLP or sequencing for Phase II, and real-time PCR (TaqMan^®^ SNP Genotyping Assays, Applied Biosystem) for Phase III, which allows the semi-automation of these determinations. All these techniques proved to be reproducible and stable under the conditions of the study. The reliability of the techniques used for genotyping in the different phases of the study has been proved using internal quality controls through different methods: repeated measurements of randomized samples, double-blinded reading of random samples, introduction of positive and negative controls, and random doubled testing of samples by both techniques. We obtained consistent results for any of the techniques used.

### Assessment during the follow-up

#### Training control

Feedbacks for training loads were done once a month with the Rate of Perceived Exertion (RPE) to subjectively evaluate each session and determine where the participant considered the intensity to be at, following a similar methodology previously used [69].

#### Physical activity control

PA was assessed as described above once a month. All subjects were instructed to continue their habitual daily activities as before the intervention period and were provided with a PA diary to log the type, duration, and intensity of any PA or exercise undertaken during the intervention.

#### Body weight control

BW was measured as described earlier every fifteen days at the Sports Center. Subjects included in group C used their own scales to monitor BW at home during the intervention.

#### Dietary intake control

A dietician interviewed each participant at baseline, and at 3 and 6 months after the start of the intervention. All subjects were instructed about how to record their dietary intake using a daily log, and given recommended portion sizes and information on possible food swaps. In addition, voluntary group nutrition education sessions were given by the dieticians. The goal was to equip the participants with the necessary knowledge and skills to achieve gradual, permanent behavioural changes.

### Statistical analysis

The main independent variables of the study were: intervention group, age, gender, measurement (baseline – post) and BMI classification (overweight or obese). The delta percentage was calculated thought the standard formula: change (%) = [(post-test score − pre-test score)/pre-test score]*100. The power calculated previously to find significant differences between groups was 0.8 to fat mass (%).

Standard statistical methods will be used for the calculation of the means and standard deviation for all dependent variables. The statistical analysis will be as follows: 1) Univariate descriptive analysis, study of data distribution, basic statistics such as central and dispersion values. Pair comparison tests with previous analysis of the homogeneity of variance will be used. Pearson correlation coefficients, chi-squared tests and exact probability calculations will be also performed to study the relationship between quantitative and qualitative variables, respectively; 2) General lineal models, such a multivariate analysis (MANOVA) or two way analysis of variance (ANOVA) for repeated measures, will be used to determine differences among the four interventions groups and between baseline and post-training values. Compound symmetry, or sphericity, will be verified by the Mauchly test. When the assumption of sphericity would not be met, the significance of F ratios will be adjusted according to the Greenhouse-Geisser procedure. Multiple comparisons of ANOVAs will be made with the Bonferroni post -hoc test.

The analysis of the data will be done using statistical package SPSS (SPSS Inc., Chicago, Illinois, USA). The significant level will be set at α = 0.05.

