### Population and sample size estimation

The estimation of the sample size was calculated to detect a main effect of the treatment on the percentage of body fat with a 80% statistical power at 5% significance, assuming a 0.80 correlation between repeated measures [43]. The initial calculated sample size per intervention group (n = 22) permits the detection of a large effect size (Cohen’s d = −0.8), as observed in a previous investigation [43].

The initial adjustment of sample size for dropouts carried out used a maximum of 25% of dropouts in each group [37]. Adjusted dropouts sample = n (1/1-R), where n = number of subjects not lost, and R = expected proportion for dropouts. With our data, the initial necessary sample size was: 88 (1 / 1–0.25) = 118 subjects or 29/30 in each intervention group, this being applicable for both the overweight and the obese interventions groups. A total of two hundred thirty nine people initiated the study, completing it 180 (75.3%), which supposed 59 dropouts for different reasons. For personal reasons 17 (28.8%), low exercise adherence 3 (5.1%), low diet adherence 6 (10.2%), job change 6 (10.2%), and lost interest 27 (45.8%).

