### Recruitment of the subjects

Subjects were recruited by means of diverse advertisements published in the media and the applicants filtered using different criteria. The voluntary subjects who fulfilled the inclusion criteria and passed the baseline physical examination were stratified by age ranges and body mass index (BMI), and randomized into the different intervention groups (Figure 1).

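### The plan does not say which ANOVA term is the treatment effect, and its sample size points to the group term averaged over baseline and post, which halves the effect; a baseline-adjusted ANCOVA should be named

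*Protocol article*

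**What the plan says.** The Statistical analysis section of the protocol article lists intervention group, age, gender, measurement (two levels, baseline and post) and BMI class as the main independent variables. It then offers general linear models, with MANOVA or two-way repeated-measures ANOVA as examples; a "two way analysis of variance (ANOVA) for repeated measures, will be used to determine differences among the four interventions groups". The same model is to compare values before and after training. "Compound symmetry, or sphericity, will be verified by the Mauchly test", with a Greenhouse-Geisser correction if needed and Bonferroni post-hoc comparisons. "The significant level will be set at α = 0.05". Percent change is defined ("The delta percentage was calculated thought the standard formula"), but is not assigned to any test.

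Neither the group-by-time interaction nor a baseline covariate is mentioned.

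The section on population and sample size says that the trial was sized to "detect a main effect of the treatment on the percentage of body fat with a 80% statistical power at 5% significance". The calculation takes the correlation of the two measurements as 0.80, and the article states that 22 per group "permits the detection of a large effect size" (Cohen's d of 0.8 in absolute value). Under Recruitment of the subjects, eligible volunteers "were stratified by age ranges and body mass index (BMI), and randomized into the different intervention groups".

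**The concern.** A two-way repeated-measures ANOVA of group and time gives two terms that involve the arms. The group term compares the arms on the average of the baseline and post values. The group-by-time interaction compares them on change. Randomised arms have no expected difference at baseline, so averaging baseline in dilutes the treatment effect.

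The plan asks the model for differences among the four groups without naming a term, and the sample size section speaks of a main effect. An analyst who follows that wording could read the diluted term as the treatment test. Even when the interaction is used, the model gives up some precision, because regressing on baseline is more efficient than subtracting it. The completers number 84 overweight and 96 obese, or on average 21 and 24 per arm, so avoidable imprecision matters.

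**Working it through.** **Inputs.** From the sample size section: 22 per group, |d| = 0.8, correlation ρ = 0.80, 80% power, 5% significance. Assumed, because the article does not say: two-sided testing, equal variances at both times, a common baseline slope, and d in SDs of percent fat. The other reading of d is taken up in step 5.

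**1. Reproducing the plan's 22.** Use n = 2 × F × ((1.960 + 0.842)/0.8)², where F is the variance of the quantity compared, in units of the outcome variance.

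| Quantity compared | F at ρ = 0.80 | n per group |
|---|---|---|
| Mean of baseline and post (group term) | (1 + ρ)/2 = 0.90 | 22.07 |
| Post value only | 1 | 24.5 |
| Change (group-by-time interaction) | 2(1 − ρ) = 0.40 | 9.8 |
| Post adjusted for baseline (ANCOVA) | 1 − ρ² = 0.36 | 8.8 |

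The group term gives the stated figure. Strict rounding up would give 23, and a t-based calculation 24. A four-arm F test of the group term, with one arm differing by 0.8 SD, gives exactly 22.

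**2. What that term does to a treatment effect.** The calculation takes the averaged values to differ by 0.8 SD. A treatment that produces a 0.8 SD difference at post, with none at baseline, gives (0 + 0.8)/2 = 0.4 SD on the average.

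**3. Pairwise power at 22 per arm, two-sided 0.05, unadjusted.** The noncentrality is effect/√(2F/22).

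| Test | Effect | Noncentrality | Power (noncentral t) |
|---|---|---|---|
| Group term | 0.4 | 0.4/√(1.8/22) = 1.40 | 28% |
| Interaction | 0.8 | 0.8/√(0.8/22) = 4.20 | 98% |
| ANCOVA | 0.8 | 0.8/√(0.72/22) = 4.42 | 99% |

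A simulation of the four-arm F tests (4,000 runs, 22 per arm, one arm 0.8 SD apart at post) gave 24.9%, 99.1% and 99.8%. At 0.5 SD it gave 12.6%, 76.4% and 81.6%. With no effect all three rejected in about 5% of runs (4.4%, 5.7%, 4.9%).

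**4. ANCOVA against the interaction.** The variance ratio is (1 − ρ²)/(2(1 − ρ)) = (1 + ρ)/2. At ρ = 0.80 it is 0.36/0.40 = 0.90, or 10% less residual variance. At the difference where the interaction has 80% power (0.534 SD, normal approximation), ANCOVA has 84.0%. The plan gives no correlation for other outcomes. If it were 0.7 the ratio would be 0.85, and at 0.5 it would be 0.75.

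**5. If d is in SDs of change.** Then 0.8 change-SDs is 0.8 × √0.40 = 0.506 SD of percent fat. Power by the normal approximation at 22 per arm is 75.6% for the interaction and 79.9% for ANCOVA. The group term sees 0.253 SD, with noncentrality 0.253/√(1.8/22) = 0.88 and power about 14%.

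**6. Sphericity.** Two levels leave one within-subject contrast. Mauchly's W is then 1 with 0 degrees of freedom, and the Greenhouse-Geisser epsilon is 1 for any covariance matrix.

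**The case against.** The best defence is that the plan never makes the group term the decision term. Anyone used to pre/post designs would read the interaction, which is unbiased and well powered. On that reading ANCOVA is an improvement and not a correction: about 1 power point at 0.8 SD and about 4 near 80% power. This stands, and it limits the size of the point. It does not settle which term is meant, because the sample size wording and arithmetic point to the group term.

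The arithmetic is not conclusive by itself. Because the ANCOVA-to-change variance ratio is also 0.90, a baseline-adjusted test with d in change SDs would give the same 22.07. But the article mentions no covariate and does speak of a main effect.

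Several stronger readings are tempting and are not supported:

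- *The planned analysis is biased, or the trial has only 28% power.* The interaction is valid; 28% applies only if the averaged group term is taken as the test.
- *The stratification factors are left out.* Age, gender and BMI class are listed as independent variables, and the two-way model is only an example. What is unclear is which factors enter which model.
- *Percent change is the tested outcome.* The article only defines it.
- *Adjusting for sex brings a large gain because sex explains much of baseline percent fat.* Baseline adjustment already absorbs most of a stable sex difference. What sex, age or BMI add after that cannot be computed from the document.
- *The sphericity check damages the analysis.* With two times it changes no p-value. Weight, activity and diet were measured more often, but the plan defines its repeated factor as baseline and post only.

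**Conclusion.** The point holds as a specification gap with a modest efficiency gain attached. The treatment term is unnamed, and the document's own sample size wording steers towards a term that halves a post-intervention difference. If that term were used, pairwise power at 22 per arm would be about 28% where the interaction has about 98%, with d in raw SDs and two-sided unadjusted 0.05. If d is in change SDs, the contrast is about 14% against 76%.

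If the interaction is what is meant, the test is sound, and baseline adjustment saves 10% of residual variance at the plan's correlation. The saving is larger only for outcomes whose pre/post correlation is lower, and the article gives no such correlation. The sphericity step is redundant and harmless.

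**What to change.** State, for each pre/post outcome and within each BMI cohort, an ANCOVA of the post-intervention value on arm, baseline value and the stratification factors (age and BMI, as strata or continuous), optionally with sex. Report Bonferroni-adjusted arm differences with confidence intervals. State explicitly that the group main effect averaged over time is not the treatment test. If the repeated-measures ANOVA is kept, name the group-by-time interaction as the treatment test. Drop the Mauchly and Greenhouse-Geisser step for two-time outcomes, and say whether percent change is descriptive only.

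The cost is wording. No extra participants or measurements are needed. The model spends one degree of freedom on baseline and a few on the other covariates, which is negligible with the planned 88 completers per cohort. The article leaves the effectiveness analyses to later publications, so the statement can be made there.
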